### Data collection

The principal investigator will screen the eligibility of potential participants. For these eligible individuals, an Information Sheet of the study will be provided, and written informed consent will be sought. Information related to demographics and health background will then be collected (Appendix 3). All primary and secondary outcomes will be measured at baseline (T0), 2 months (T1; completion of intervention), and 3 months following the completion of the intervention (T2). All assessment will be conducted during the “on” state of medications to minimize motor fluctuations among participants. Participants will be instructed to follow their normal medication schedule and physical activity and not to start any new, instructor-led exercise program throughout the study period.

### Data analysis

Descriptive statistics will be used to summarize the demographic, health conditions and clinical outcomes of the participants at three different time points. Normality of the variables will be assessed using the skewness statistic and normal probability plot. The two treatment groups will be examined, at baseline (T0), after the completion of intervention (T1), and 3 months after the completion of intervention (T2), for the changes in psychological distress, motor symptoms, mobility and balance, spiritual wellbeing, and HRQoL among participants. The intention-to-treat principle will be applied in all analyses. The intervention arm will be compared against the control for all primary analysis. Generalized estimating equation (GEE) models, specific with first-order, auto-regressive structure, will be used to assess the differential change of each primary outcome variable (HADS) and secondary outcome variable (MDS-UPDRS-III, TUG, HWS, and PDQ-8), across different time points between the two groups. Completers and noncompleters will be compared to examine any difference in demographic characteristics and health conditions. Prespecified subgroup analyses by gender, level of education, disease staging, and the presence of psychological distress will be conducted. IBM SPSS 22.0 software will be used for statistical analysis. All statistical tests will be two-tailed and statistical significance will be set at 0.05. The final report will follow the CONSORT 2010 guidelines as well as its extension to nonpharmacological interventions.

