**Methods:**

A community-based, single-blind, randomized trial will be conducted. A total of 126 subjects will be recruited and randomly divided into yoga (*n* = 63) or stretching and resistance exercise (*n* = 63) groups. For 8 weeks, the yoga group will receive a weekly 90-min session of yoga, and the control group will receive a weekly 60-min session of stretching and resistance exercises. The primary outcome will be the level of psychological distress measured using the Hospital Anxiety and Depression Scale. The secondary outcomes will include the severity of motor symptoms measured by the Movement Disorders Society – Unified Parkinson’s Disease Scale − Part III Motor Examination; mobility, balance, and fall risk measured by the Timed Up and Go test; spiritual wellbeing measured by the Holistic Wellbeing Scale; and HRQoL measured by the Parkinson’s Disease Questionnaire-8. Assessment will be conducted at baseline, 8th, and 20th weeks of follow-ups.

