### Sample size

According to a meta-analysis of the effects of yoga on depression compared with aerobic exercise, a moderate effect size of 0.59 was reported for individuals with elevated levels of depression.

In addition, a moderate-to-large effect size of 0.79 on anxiety was found when comparing yoga with relaxation [26]. To anticipate the effect size of at least 0.59 for our primary outcomes (depression and anxiety) and using the power analysis software Gpower 3.1, 47 subjects per arm give a two-arm RCT 80% power to detect an effect size of at least 0.59 at 5% level of significance. Considering previous RCTs of mind-body interventions among people with PD [20], an attrition rate of 25% is taken into consideration. Therefore, 126 subjects with 63 per arm will be recruited.

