#### Attrition and missing data

Regarding attrition and missing data, an attrition rate of 25% is considered in this trial, and we will monitor the progress of the trial with respect to this target. To reduce attrition and missing data, the importance of full and complete participation in the trial, regardless of the treatment assignment, will be conveyed to the study team members and participants. Follow-ups will be arranged at participants’ convenience to minimize the burden of data collection. Participants will be contacted on telephone for follow-up arrangement, and two follow-up reminders will be delivered to participants, via telephone call or WhatsApp message at 2 weeks, and 1 day before follow-up. In order to facilitate a positive study experience among participants, all participants will be attentively followed up. All study procedures will be described clearly to the participants, and their performance assessment and its corresponding health implications will be explained individually at the end of each follow-up by the assessor. Contact information of participants will be kept up to date and reasons of dropout will be documented [40].

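### The planned AR(1) GEE appears to compare raw HADS change between arms; using baseline HADS as an adjustment, with an unstructured covariance, would be more precise and less exposed to selective dropout at almost no cost

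*Protocol article*

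**What the plan says.** The Data analysis section of the protocol article names the model for HADS and every secondary outcome: "Generalized estimating equation (GEE) models, specific with first-order, auto-regressive structure, will be used to assess the differential change" across time points between the two groups. The same section lists the time points: "The two treatment groups will be examined, at baseline (T0), after the completion of intervention (T1), and 3 months after the completion of intervention (T2". T0 is thus one of the analysed occasions, and no covariate is named. On testing it says "All statistical tests will be two-tailed and statistical significance will be set at 0.05". The Abstract gives the visit times: "Assessment will be conducted at baseline, 8th, and 20th weeks of follow-ups".

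The Sample size section says "47 subjects per arm give a two-arm RCT 80% power to detect an effect size of at least 0.59 at 5% level of significance" and then "Therefore, 126 subjects with 63 per arm will be recruited" to allow for attrition. The Attrition and missing data section repeats that "an attrition rate of 25% is considered in this trial". It then describes reminders, flexible follow-up and the recording of reasons for dropout. In the analysis, the only step aimed at dropout is a comparison of completers with noncompleters on demographic characteristics and health conditions.

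**The concern.** Two features of the stated model deserve a second look.

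The first is precision. A group-by-time model in which each arm has its own free mean at T0 estimates the difference between arms in raw change from baseline. In a randomized trial the true arm means at T0 are equal, and a model that uses this fact is never less precise. The article does not use it, although baseline HADS is measured on everyone.

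The second is dropout. First-order autoregression by visit order forces corr(T0,T1) = corr(T1,T2) and sets corr(T0,T2) to the square of that value. If the real correlations differ, an unweighted GEE is generally consistent only when dropout is completely at random. Participants know their arm, and the article itself lists attrition among the biases of its single-blind design. Raising the sample size replaces lost numbers but does not correct bias, and nor does comparing completers with noncompleters.

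At stake are free precision on the primary outcome and some protection of the T2 contrast.

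**Working it through.** **Inputs.** From the article: effect size d = 0.59, two-sided 5%, 80% power, 47 per arm, 25% attrition, 63 per arm (126 in total), visits at weeks 0, 8 and 20. Not in the article: the baseline-to-follow-up correlation rho. The Pilot study section gives an SD of 4.16 for the HADS change but no baseline SD, so rho cannot be derived. It is assumed to lie between 0.3 and 0.8. It is also assumed that 0.59 is standardized on the SD of a single score and that this SD is the same at each visit.

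**The plan's own figure.** The exact two-sample t calculation gives 79.9% power at 46 per arm and 80.8% at 47. Then 47/0.75 = 62.7, rounded up to 63, and 2 × 63 = 126. All three figures reproduce.

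**Precision.** Variance of the arm contrast at one follow-up, relative to comparing follow-up scores alone:

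- change from baseline: 2(1 − rho)
- baseline-adjusted: 1 − rho²
- ratio, adjusted to change: (1 − rho²) / [2(1 − rho)] = (1 + rho)/2

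Power comes from the noncentral t with 47 per arm and d divided by the square root of the variance factor. At rho 0.3, for example, 0.59/√1.40 = 0.499 for change and 0.59/√0.91 = 0.618 adjusted.

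| rho (assumed) | Variance ratio | Power, change | Power, adjusted | n per arm for 80%: change / adjusted |
|---|---|---|---|---|
| 0.3 | 0.65 | 66.7% | 84.3% | 65 / 43 |
| 0.4 | 0.70 | 73.4% | 87.0% | 56 / 39 |
| 0.5 | 0.75 | 80.8% | 90.5% | 47 / 35 |
| 0.6 | 0.80 | 88.6% | 94.3% | 38 / 30 |
| 0.7 | 0.85 | 95.5% | 97.7% | 29 / 24 |
| 0.8 | 0.90 | 99.4% | 99.7% | 20 / 18 |

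At rho 0.5 the change analysis has exactly the planned power. Below 0.5 it has less, above 0.5 more. The adjusted analysis has more power than the change analysis in every row.

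**Visit spacing.** Simulated trials (63 per arm, 1,000 runs per scenario, group-by-time means, robust standard errors) compared three working correlations: AR(1) by visit order, AR(1) with the true 1:1.5 spacing, and unstructured.

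- Complete data: identical estimates and power for all three.
- 25% dropout completely at random: T2 power of 77.6% to 77.9% when the true correlation is 0.7 over 8 weeks and decays with time, and 89.2% to 90.4% with a constant correlation of 0.6.

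**Dropout related to earlier scores.** Same simulation, SD units, about 24% to 30% missing at T2.

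- Same mechanism in both arms: T2 estimates of −0.58 to −0.59 for a true −0.59, so no visible bias.
- Opposite mechanisms by arm, constant correlation 0.6: AR(1) by visit order gave −0.515 for a true −0.59 and +0.081 for a true 0, with 7.7% rejection under the null. Unstructured gave −0.574 and +0.022. AR(1) with the true spacing gave −0.451 and +0.135, which is worse.
- Opposite mechanisms by arm, decaying correlation: AR(1) by visit order gave −0.592 and +0.006; unstructured gave −0.573 and +0.020.

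A separate large-sample simulation, with no true effect, opposite mechanisms and corr(T0,T2) from 0.45 to 0.6, gave an AR(1) bias at T2 of 0.05 to 0.07 SD with strong dependence on the last score and 0.01 to 0.02 SD with weaker dependence. The unstructured likelihood model was off by at most 0.01 SD.

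For scale, 0.081 SD is 0.081/0.183 = 0.44 of the mean standard error of that contrast.

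**The case against.** The article does not write out the mean model. Covariates, and whether the T0 means are free or constrained, may be settled in a full protocol or analysis plan that is not shown, as may the missing-data method. A group-by-time GEE is also a valid analysis of a randomized trial, and it does not need normality. All of this stands. The point is therefore an improvement on a model that the article does fix, not a charge of omission.

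Four stronger readings are tempting, and the document supports none of them.

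- *Baseline HADS is left out.* It is not: T0 is one of the analysed time points. The issue is how baseline is used.
- *Unequal spacing does harm.* Visits are indeed 8 and 12 weeks apart, but the working structure made no difference with complete data and about one point of power at most under completely random dropout. Respacing AR(1) made the bias worse in the hostile scenarios. Spacing is not the mechanism.
- *The trial is underpowered.* That needs rho below about 0.5, and the article gives no rho. If HADS scores are fairly stable within a person, change-analysis power meets or exceeds 80%.
- *The T2 result will be biased.* Bias appeared only with dropout running in opposite directions by arm, which is an assumption. Both arms have the same number of sessions and assessments, and the follow-up reminders are for all participants. With decaying correlation the stated AR(1) model showed essentially no bias even then.

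**Conclusion.** The point holds as a worthwhile improvement to the primary analysis. The gain in precision is certain in direction: the variance of the arm contrast is 10% to 35% smaller with baseline adjustment for rho of 0.8 to 0.3. Only its size depends on the unknown rho, and in power it runs from 17.6 points at rho 0.3 (84.3 − 66.7) to 0.3 points at rho 0.8 (99.7 − 99.4). This rests on reading the stated model as a raw-change contrast, which the wording suggests but does not spell out.

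The dropout part is a risk, not an established consequence. It is modest, about 0.01 to 0.08 SD at T2 under assumed arm-specific mechanisms, and not visible when both arms share a mechanism. The loss of numbers is already covered by recruiting 63 per arm.

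**What to change.** Analyse HADS with a likelihood-based repeated-measures model (the MIXED procedure in the SPSS software already named) over T0, T1 and T2, with an unstructured covariance and the arm means constrained equal at T0, or with baseline HADS as a covariate. Report the arm difference at T1 and at T2. With the constrained baseline, every participant with any observation contributes, and the model is valid if data are missing at random.

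If the GEE is preferred, add baseline HADS as a covariate and use an unstructured working correlation. That recovers the precision and removed most of the bias in the constant-correlation scenario above, although an unweighted GEE still lacks a general guarantee under missing at random.

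The cost is a change of wording and model syntax; no new data or visits are needed. An unstructured covariance for three visits has six parameters, which 126 participants can support. The one small downside is that the likelihood model relies on approximate normality of a bounded score. The skewness statistic and normal probability plot already planned can be used to check this.

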### Ethical considerations

#### Autonomy, privacy, and confidentiality

Ethics approval was obtained from The Joint Chinese University of Hong Kong – New Territories East Cluster Clinical Research Ethics Committee (2016.323–T) in August 2016. The study was registered in the WHO Primary Registry – Chinese Clinical Trials Registry (ChiCTR) (CUHK_CCRB00522) in August 2016. Written informed consent will be obtained from eligible participants before any assessment or intervention. The participation will be voluntary and participants will be allowed to withdraw from the study at any time point. Confidentially will be maintained using unique identification numbers of subjects. All data will be kept in a locked and secured cabinet, and access will be restricted to the research staff. This protocol is stated in compliance with the Declaration of Helsinki.

#### Risks and safety

Yoga is generally regarded as safe, and adverse events are rare. The major potential risks of yoga are muscle strains or injuries. Therefore, adequate warm-up and cool-down exercises are emphasized in this program. Props, such as towel, chair, and wall, will be used to support participants toward some more challenging poses. Apart from that, each posture of this yoga program has been tailor-made and reviewed by the expert panel to ensure that it will be delivered in a progressive and safe manner for individuals with mild-to-moderate PD. The interveners of both arms will have at least 2 years of teaching experience among individuals with chronic illnesses. In addition, clinical trial insurance will be purchased for all participants in the experimental group. Participants will be instructed to report any unexpected or unusual symptom to the principal investigator. A project adverse log will be used to document any adverse events. Any major serious adverse event will be reported immediately to the Ethics Committee. No formal stopping rules will be established in advance for efficacy. The trial will be stopped only if there is an unacceptable risk of serious adverse events in one or both of the treatment arms. In this case, investigators will recommend terminating either or both of the arms of the entire study.

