#### Adherence

All participants will be instructed to follow their normal medication schedule and physical activity and not to start any new instructor-led exercise program throughout the study period. All classes will be held at local community facilities. Picture-based education booklets with enlarged picture guides will be provided to participants to facilitate home-based practice (see Additional file 2: Yoga Educational Booklet). All participants will also be instructed to perform a 20-min, home-based practice twice a week. A self-reported activity log will be provided to monitor participants’ adherence to home-based practice. Class attendance will be checked by the instructor. Reasons for absenteeism will be also documented and verified by the research coordinator.

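### The instruction telling participants what to report is narrower than the harms the plan foresees and the log it means to fill, so non-serious harms may be under-counted

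*Protocol article*

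**What the plan says.** Four statements in the Risks and safety section of the protocol article bear on this.

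- Foreseen harm: "The major potential risks of yoga are muscle strains or injuries". No corresponding risk is described for the stretching and resistance arm.
- Instruction to participants: "Participants will be instructed to report any unexpected or unusual symptom to the principal investigator".
- Recording: "A project adverse log will be used to document any adverse events".
- Serious events: "Any major serious adverse event will be reported immediately to the Ethics Committee".

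Two other sections give incidental routes. Under Adherence, attendance is checked at class, and "Reasons for absenteeism will be also documented and verified by the research coordinator". Under Attrition and missing data, reasons for dropping out are recorded. Adherence also provides a self-completed record of home practice: "A self-reported activity log will be provided". Its stated purpose is to monitor adherence, not harms.

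**The concern.** The article does not leave this matter open. It states what participants are asked to report, and what it states does not fit its neighbours. The plan foresees strains and injuries, and wants every adverse event in the log. Yet it asks participants only for symptoms that strike them as unforeseen or out of the ordinary. Someone who aches or pulls a muscle after a new exercise programme may reasonably judge that this is neither.

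At stake is what the trial can later say about harm. The Discussion already presents yoga as attractive partly because its side effects are minimal. A log with few or no entries would be weak support for that if the instruction feeding it discouraged the commonest kind of entry. Participants in both arms know their allocation and only yoga's risks are described, so the inclination to report could also differ between arms.

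**Working it through.** **Side-by-side reading.** No adverse-event rate or capture rate is given, so the main check is of the text.

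1. *Scope of the log:* any adverse event, with no limit to unexpected events and none by arm.
2. *Scope of the instruction:* unexpected or unusual symptoms, raised by the participant with the principal investigator.
3. *Harms foreseen:* strains and injuries. These fall inside (1) and, read literally, need not fall inside (2).
4. *Can the other stated routes fill the gap?*
   - Reasons for absence catch a harm only if it makes someone miss a class. Classes end at week 8.
   - Reasons for dropout catch a harm only if it makes someone leave.
   - Reporting to the Ethics Committee covers serious events, once they are known.
   - The log stores events but does not elicit them.
5. *Where the gap is widest:*
   - Home practice is suggested twice a week for 8 weeks, 2 × 8 = 16 sessions, against 8 classes. No instructor is present at home.
   - T2 falls 3 months after the classes end (Data collection), when there is no attendance check.

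**Is harm known to be too rare to matter?** The Pilot study section reports no adverse events in 10 yoga participants. The one-sided 95% upper limit for 0 of 10 is 1 − 0.05^(1/10) = 0.259. The pilot is compatible with a true risk up to 25.9%. It had no control arm, and the same section says classes have since been lengthened from 60 to 90 minutes.

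**Illustrations of size.** Only the 63 per arm comes from the protocol (Sample size). Every capture rate and event risk below is an assumption.

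*No participants with an event logged among 63.* The one-sided 95% upper limit on the logged risk is 1 − 0.05^(1/63) = 0.0464. If a fraction c of affected participants is captured, the compatible true risk is 0.0464/c.

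| Assumed capture c | Compatible true risk |
|---|---|
| 1.00 | 4.6% |
| 0.50 | 0.0464/0.50 = 9.3% |
| 0.25 | 0.0464/0.25 = 18.6% |

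*Expected log entries per arm, 63 × risk × capture:*

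| Assumed true risk | Capture 100% | Capture 50% | Capture 30% |
|---|---|---|---|
| 10% | 6.3 | 3.2 | 1.9 |
| 20% | 12.6 | 6.3 | 3.8 |
| 30% | 18.9 | 9.4 | 5.7 |

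*Unequal capture with equal true risk.* At 20% risk in both arms and capture of 80% against 40%, the log would show 63 × 0.20 × 0.80 = 10.1 against 63 × 0.20 × 0.40 = 5.0, a spurious ratio of 2.0 (0.5 if reversed). That ratio is simply 80/40. It shows how the mechanism would work and is not evidence that it operates here.

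No figure in the sample-size section is affected.

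**The case against.** The strongest reply is that the log covers any event and that a lay participant would naturally call a new strain unusual, so nothing named is excluded. In part this stands: the wording may discourage some reports, but it forbids none, and under-counting is a risk rather than a certainty. It does not remove the mismatch, because a log can hold only what reaches it.

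Several stronger readings are tempting, and the documents do not support them.

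- *Harms reach the trial only if volunteered.* Not so: serious events have a reporting duty, and reasons for absence and dropout are recorded.
- *Insurance gives only the yoga arm a reason to report.* The article does say "clinical trial insurance will be purchased for all participants in the experimental group". It does not link insurance to reporting or say that participants are told of it, and no stated reporting rule differs by arm.
- *The stopping decision is compromised.* The text is "The trial will be stopped only if there is an unacceptable risk of serious adverse events in one or both of the treatment arms". That turns on serious events, while the gap shown here concerns mainly non-serious ones.
- *Falls are left out.* The article lists no fall count; the Timed Up and Go test measures fall risk. But a condensed article may leave event definitions and fall recording to the full protocol, so their absence is not part of this finding.
- *A planned comparison is corrupted.* Harms are not among the listed outcomes or analyses.

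It is also fair to say that a preference for solicited over spontaneous collection would not by itself be a finding. The finding is that the collection rule the article does state is worded more narrowly than its own purpose.

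**Conclusion.** The point holds in a limited form. The stated instruction is narrower than both the foreseen harms and the log it feeds, and the remaining routes do not elicit non-serious harms, particularly at home and after week 8. Harms may be under-counted. The amount cannot be computed from the article, and the illustrative figures depend wholly on assumed capture rates. A difference in reporting between arms is plausible from unblinded participation and the yoga-only description of risk, but it is not demonstrated.

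The conclusion assumes that participants receive the instruction in roughly the words printed and that the full protocol does not already replace it with a broader question. If it does, aligning the article's sentence is all that remains. The primary analysis is untouched. The consequence is confined to what the trial can say about safety.

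**What to change.** 1. Reword the instruction so that participants in both arms are asked to report any adverse event, whether or not expected, expressly including strains, injuries and falls.
2. Add one fixed question, identically worded in both arms, to the existing home-practice log.
3. Put the same question to every participant at T1 and T2 on a self-completed form that the blinded assessor does not see. The T2 form should cover the whole interval since T1, because the article does not say that the log continues after the classes end.
4. Keep spontaneous reports as a supplement, and report counts by arm.

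The cost is one extra item on a log already in use and a short form at two visits already scheduled. Raw event counts will rise in both arms, and the report should explain that solicited counts run higher than spontaneous ones. Answers for the interval between T1 and T2 would rest on about three months' recall.
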